### Primary outcome measure

#### Mental wellbeing

The Dutch version of the Mental Health Continuum - Short Form (MHC-SF) will be administered to measure the current psychological, emotional and social wellbeing during the last month [49, 74]. The MHC-SF is a 14-item self-report questionnaire that consists of a 5-point Likert scale. The psychometric features of the MHC-SF are good. There is evidence for a high internal and moderate test-retest reliability and good convergent and discriminant validity [74]. The mean score of the psychological, emotional and social wellbeing scales - the (positive) mental wellbeing score – will be the primary outcome of this study. Assessment of the primary outcome variable will be conducted at baseline and 3, 6, 9, 12 and 18 months after baseline. The mean difference of the mental wellbeing score between groups over time - from baseline to assessment at 12 months - will be chosen as the main outcome measure of this study. Table 1 provides an overview of all instruments and the corresponding time of assessment.

### Key secondary outcome measures

#### Psychiatric functioning

The Health of the Nations Outcome Scales (HoNOS) is a 12-item, 4-point Likert-type scale, for the assessment of general and psychiatric functioning of people with severe mental problems [48, 75, 76]. The HoNOS consists of four subscales: behavioral problems, deficiencies, symptomatology and social problems. The HoNOS is widely used by clinicians. It is a valid instrument for the assessment of the effectiveness of mental health services, with good overall interrater and test-retest reliability, criterion validity and concurrent validity [48, 77]. The Dutch version of the HoNOS will be completed by a researcher at baseline and follow-up assessments at 3, 6, 9, 12 and 18 months after baseline, based on observations during assessment and information from the electronic patient file.

In addition, the number of renewed hospitalizations will be monitored throughout the study. We will ask participants whether and how frequently they have been hospitalized at all assessments. The number of hospitalizations during the study will also be gathered from electronic patient files.

#### Criminal recidivism

Self-reported criminal recidivism will be measured with 29 items of the Self-Reported Delinquency scale (SRD) [78]. Participants are asked if they have committed a list of 29 specific criminal activities (yes/no). Furthermore, they are asked to make an estimation about the number of total criminal activities throughout their lives and in the past 6 months. The criminal activities vary from minor to rare and serious offences. A total delinquency score can be obtained and the total delinquency score can also be divided into five subscale scores: public order offenses, property crimes, violent crimes, drug-related crimes and owning illegal weapons. Self-report approaches of criminal recidivism have demonstrated acceptable reliability and validity [79]. The SRD will be measured at baseline and 12 and 18 months after baseline assessment.

Additionally, information about the type, number, severity and time of arrests and offenses will be collected from the International Police Information Service (IPOL) and the Justice Documentation System (JDS) of the Dutch Ministry of Safety and Justice [80]. We will collect data from these records at 12 and 36 months after baseline assessment. Furthermore, the number of renewed incarcerations will be monitored throughout the study. We will ask participants whether and how frequently they have been incarcerated at all assessments. The number of incarcerations during the study will also be gathered from electronic patient files.

### Other secondary outcome measures

#### Substance abuse

Two chapters of the Measurement in the Addictions for Triage and Evaluation (MATE 2.1) [81] will be used for the assessment of alcohol and drug use as well as alcohol and drug abuse or dependency according to the DSM-IV-TR. Chapter one of the MATE 2.1 will be assessed at baseline and 3, 6, 9, 12 and 18 months after baseline, to measure the prevalence, frequency and average amount of an extensive list of substances (e.g. nicotine, alcohol, tranquillizers, drugs) in the last 30 days. In addition, the onset and duration of frequent substance use and the primary, secondary and tertiary problematic substances can be determined. Chapter four of the MATE 2.1 consists of 11 questions (yes/no) that can be used to determine alcohol and drug abuse or dependency in the past 12 months. Therefore, chapter four will be assessed at baseline, and 12 and 18 months after baseline. The MATE 2.1 has acceptable validity and reliability scores [82].

#### Quality of life

Quality of life will be measured with the Dutch version of the Manchester Short Assessment of Quality of Life (MANSA), a 16-item 7-point Likert-type self-report questionnaire [46]. The MANSA consist of 12 Likert-type questions that are related to important domains of life such as physical health, mental health, safety, social relationships, leisure activities, work and finance. Additionally, four yes/no-questions regarding victimization, delinquent behavior and friendships are included. The questionnaire demonstrated adequate psychometric properties [46]. The MANSA will be measured at baseline, and 3, 6, 9, 12 and 18 months after baseline assessment.

#### Social network

The size and quality of the social support network is measured with a self-developed interview based on the Modified Multiple Generator (MMG) [83] and Name Generator/Interpreter method (NGI) [84]. The NGI method is widely used in sociological research to investigate the size and quality of different type of social networks and changes in social networks [83, 85]. The MMG approach is a time-saving alternative of the NGI method, and therefore more appropriate for the current study. Two widely used name generator questions (“who are the people with whom you discuss matters important to you” and “who are the people you really enjoy socializing with”) are administered to determine the size of the social support network. If participants report more than five names, they will be asked to mention the five most important network members. Additionally, name interpreter questions are administered to measure the demographic characteristics of network members, the quality of the relationships and contact frequencies. Even though content validity of the MMG approach is less strong, when compared with the full NGI method, the MMG is found to be an acceptable alternative [83]. The instrument will be administered at baseline and 12 and 18 months after baseline.

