Care professionals of all patients included in the study (TAU and FNC) will be stimulated by the research team to focus on improvement of the social network during treatment. After baseline and follow-up assessments professionals will receive an e-mail with information about a brief social network intervention and to inform them about their patient’s participation. TAU might be discontinued or finished during the course of the study, therefore the type and duration of treatment will be monitored. No treatments are withheld from patients in TAU except Forensic Network Coaching.

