During FNC, patients are matched to a forensic network coach based on their personal preferences, characteristics and interests, after an intake appointment with De Regenboog Groep.^1^ Prior to the intake, necessary information regarding the social situation of the patient is provided by a member of the research team – a procedure for which written consent is given. If matching is successful - both coach and patient agree with the match - coaching appointments take place once every 14 days. Between appointments, coaches and patients may engage in ear-to-ear or screen-to-screen contact. Within the first three to 6 months of FNC, coaches are stimulated to focus on enhancing motivation and building a working alliance with their patient. The following months will be used to draft personal goals and gaining new social experiences. Forensic network coaches visit patients in their own social environment. Besides, coaches and patients are stimulated to participate in new social activities. Evaluation of FNC takes place every 3 months and after completion of FNC, at 12 months of coaching. Both coaches and participants can decide to continue the contact after completion of FNC.

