#### Forensic network coaches

The forensic network coach is a carefully selected and trained volunteer who can be a role model and a supportive network member for the patient. The relationship between the coach and patient is called informal, meaning that coaches are non-professional volunteers that do not receive payments for their services. Furthermore, the relationship between a coach and patient is based on equivalence, confidence and liberty. Coaches are not involved in the treatment as usual.

Forensic network coaches will be provided by De Regenboog Groep, experienced in delivering coaching programs. De Regenboog Groep is responsible for the selection, training, matching and supervision of forensic network coaches. All coaches receive training in basic coaching skills, the social network intervention and on how to provide informal care within a complex forensic population. Coaches receive a manual with a worksheet of the intervention ‘Of course, a network coach!’. In addition, to ensure treatment fidelity, coaches will receive regular group supervision meetings. All coaches will be monitored by a professional of De Regenboog Groep during the coaching phase.

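### The social network measure, as described, does not exclude the coach supplied only to FNC patients, so network size and quality can shift in that arm without any change in the rest of the network

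*Protocol article*

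**What the plan says.** All references are to the protocol article.

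- **How size is obtained** (Social network). Two name-generator questions "are administered to determine the size of the social support network". One asks "who are the people with whom you discuss matters important to you"; the other asks whose company the patient really enjoys. No category of person is ruled out.
- **Five-name step** (same section). "If participants report more than five names, they will be asked to mention the five most important network members". The text does not say whether size is counted before or after this step.
- **What is recorded about each person** (same section). "name interpreter questions are administered to measure the demographic characteristics of network members, the quality of the relationships and contact frequencies". Role, such as friend, relative, professional or coach, is not listed.
- **Timing** (same section and Table 1). Baseline, 12 and 18 months.
- **The coach** (Forensic network coaches). A volunteer "who can be a role model and a supportive network member for the patient".
- **Contact** (Forensic network coaching). After a match that both sides accept, "coaching appointments take place once every 14 days", with calls in between, visits in the patient's own surroundings and encouragement to take up new social activities. Contact may continue after FNC if both wish.
- **Who gets a coach** (Treatment as usual). "No treatments are withheld from patients in TAU except Forensic Network Coaching".
- **End of coaching** (Randomization and procedure). Twelve months after baseline, when the network interview is repeated.

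**The concern.** One arm is supplied with a person who meets the wording of both questions, and the other arm is not. Professionals can also be named, but they are available to both arms, so they do not produce a one-sided shift. The coach does.

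Better social networks are the first aim listed for FNC in the Background, and this interview is the trial's direct measure of network size. If the count cannot separate the coach from contacts gained through coaching, a difference between arms at 12 months may record that the intervention was delivered rather than that it worked.

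The quality items are exposed by a second route. When a patient has more than five names, a coach among the five most important pushes another contact out of the set that is described. The document does not tell us whether that would raise or lower the quality scores.

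**Working it through.** The article gives no mean, SD, expected difference or power for network size, so there is no stated figure to reproduce. The check has two parts.

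**1. Can the coach enter the count?** The sections quoted above show that:
- the questions are open and exclude nobody;
- the coach is described as a possible network member and meets the patient regularly once matched;
- coaching runs up to the 12-month interview, and contact may continue towards 18 months;
- no listed item would identify the coach afterwards.

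Followed as written, the coach can be counted in FNC and cannot be counted in TAU.

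**2. How large could the shift be?** This is an illustration on assumed inputs, with no true effect on the rest of the network.

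Inputs from the document (Sample size): 105 randomized 1:1 with 30% drop-out, so 105 × 0.7 / 2 = 36.75, about 37 per arm.

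Assumed inputs: the number of other names is Poisson with mean μ = 2, 3 or 4. A share q of FNC patients add the coach as one extra name, with q from 0 to 100%. The test is a two-sided 5% t-test at one time point, a simplification of the planned baseline-corrected model, with 6,000 simulated trials per setting.

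Formulas for the gain in mean size:
- counted before the five-name step: gain = q × 1 name;
- counted after it: gain = q × P(X ≤ 4), because a patient with five or more other names gains nothing. P(X ≤ 4) = 7e⁻² = 0.947 for μ = 2, 16.375e⁻³ = 0.815 for μ = 3, and 34.333e⁻⁴ = 0.629 for μ = 4.

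At q = 50% the capped gain is thus 0.47, 0.41 and 0.31 names, which the simulation reproduces. Uncapped, the standardized gain is q / √(μ + q(1−q)/2). For q = 0.5 and μ = 3 this is 0.5 / √3.125 = 0.28, again matching the simulation.

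| Share naming the coach | Gain uncapped (names) | Gain capped at five, μ = 2 / 3 / 4 | Gain in SD, all settings | Chance of a false result favouring FNC |
|---|---|---|---|---|
| 0% | 0 | about 0 | 0 | 2.3–2.7% |
| 25% | 0.25 | 0.24 / 0.20 / 0.16 | 0.12–0.18 | 8–11% |
| 50% | 0.50 | 0.47 / 0.41 / 0.31 | 0.24–0.35 | 16–31% |
| 75% | 0.75 | 0.71 / 0.61 / 0.47 | 0.37–0.53 | 34–61% |
| 100% | 1.00 | 0.95 / 0.82 / 0.63 | 0.51–0.74 | 56–86% |

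The nominal chance of a false result in FNC's favour is 2.5%. The 0% row is also what holds if the coach is never counted and displaces nobody.

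**The case against.** **The rule may sit elsewhere.** The article condenses a self-developed interview into one paragraph, and nothing in it says that the coach is counted. A coding rule could stand in the interview manual or the analysis plan. This lowers certainty but does not dispose of the point. The outcome is described in some detail (questions, name limit, follow-up items, timing), and as described it admits the coach. A later exclusion rule works only if the interview identifies the coach, and no such item is listed.

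**The coach may be a genuine gain.** The Background argues for an informal tie because these patients' networks lean heavily on professionals, and the coaching relationship is unpaid and can outlast the programme. Counting a coach in whom the patient confides is a defensible choice of estimand. This stands, and it is why both counts should be reported. The choice still has to be made explicitly.

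**Month 18 is a partial safeguard.** Coaching has ended by then, so naming the coach depends largely on voluntary contact. This also stands, but only in part, and effectiveness is examined at 12 months as well.

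**Stronger readings that the document does not support:**
- A reader might infer that network size improves by construction in FNC. It does not. A gain needs a match that both sides accept and a patient who then names the coach. Unmatched FNC patients add nothing under intention-to-treat, and the five-name step may absorb part of the gain.
- A reader might set the shift against the planned effect of f = 0.20. That effect concerns the MHC-SF; none is planned for network size.
- A reader might see a circular mediation analysis. The Research aims expect benefit through better networks, but Table 1 lists social network as a secondary outcome and not among the mediators, and no mediation model using it is specified.

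**Conclusion.** The point holds in limited form. As described, the measure does not exclude the coach, so size and quality can shift in the FNC arm at 12 months, and at 18 months if contact continues, without change in the rest of the network.

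The magnitude is conditional. It is zero if nobody names the coach or the coach is excluded at coding. Under the assumed Poisson networks it reaches about a quarter to a third of an SD when half of FNC patients name the coach. At about 37 per arm, that is enough to raise the chance of a false finding well above its nominal level. The naming share and the spread of network size are assumptions; the document gives neither.

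This is a secondary outcome, measured alongside separate scales for social support, loneliness and self-sufficiency. The primary MHC-SF comparison is not affected. The point deserves correction because this outcome bears on the first aim listed for FNC.

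**What to change.** 1. Add a role code to the name-interpreter questions, used identically in both arms, with the forensic network coach as one category.
2. State whether size is counted before or after the five-name step. The order matters: if the coach is removed after the step, an FNC patient with many contacts is left with at most four, which would bias the comparison the other way.
3. Make the between-arm comparison of network size and quality with the coach excluded, and report the coach-inclusive count alongside.
4. Do not ask for a replacement name only when the coach takes one of the five places. Such a prompt would go almost only to FNC patients, from researchers who are not blinded, and could itself create a difference. If a further name is wanted, give the same prompt to every participant in both arms.

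The cost is one extra code and one analysis rule. The observed network effect may turn out smaller. Where 12-month interviews have already been held, the coach may have to be identified retrospectively, and the report should say so.

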#### Social support

Social support is measured with the Social Support List (SSL), a 41-item 4-point Likert-type self-report questionnaire [86, 87], at baseline and 12 and 18 months after baseline. The SSL consist of 34 items that refer to supportive interactions and seven items that refer to negative interactions. Positive interactions can be divided into six subscales: 1) everyday emotional support, 2) emotional support in case of problems, 3) support from the expression of validation, 4) instrumental support, 6) social companionship, and 6) informative and supportive feedback (regarding participants’ behavior). Furthermore, negative interactions can be divided into three subscales: 1) everyday support, 2) support in case of problems, and 3) support from the expression of validation. The SSL has acceptable validity and reliability scores [87].

#### Loneliness

Loneliness will be measured with the Loneliness Scale, a 11-item 5-point Likert-type self-report questionnaire [88, 89], at baseline and 12 and 18 months after baseline. The Loneliness Scale scores can be divided into emotional loneliness and social loneliness. The questionnaire demonstrated good psychometric properties [89, 90].

#### Self-sufficiency

Self-sufficiency will be measured with the Dutch version of the Self-Sufficiency Matrix (SSM-D) at baseline, and 3, 6, 9, 12 and 18 months after baseline assessment. The SSM-D is a 13-item 5-point Likert-type assessment tool of treatment outcomes [44, 45, 91, 92]. Self-sufficiency on 11 important domains of life, such as physical health, mental health, addiction, income, housing, social network, social participation and justice, are measured. The SSM-D is validated for the Dutch population [91] and demonstrated adequate psychometric properties [93, 94].

### Potential mediators and moderators

#### Diagnostic classifications

The presence of current psychiatric disorders based on the Diagnostic and Statistical Manual of Mental Disorders (Fourth edition, Text Revision and Fifth edition; DSM-IV-TR/5) and the International Classification of Diseases (Tenth revision; ICD-10) will be assessed with the MINI International Neuropsychiatric Interview-plus (MINI-plus; version 5.0) [47, 95]. The MINI-plus is a structured, clinician-administered, diagnostic instrument that consists of several sections (A-Z) that address different DSM-IV-TR and ICD-10 classifications. The MINI-plus is found to be a reliable and validated structured diagnostic instrument [95]. Section A-J, M, Q and W of the Dutch version of the MINI-plus [96] will be administered by the researchers at baseline to assess the presence of depressive disorders, suicidality, bipolar disorders, anxiety disorders, posttraumatic stress disorder, psychotic disorders, antisocial personality disorder and attention deficit hyperactivity disorder, respectively. In addition, DSM-IV-TR/5 classifications will be collected from electronic patient files at baseline.

#### Trauma

Maltreatment histories will be measured with the Childhood Trauma Questionnaire – Short Form (CTQ-SF), a 27-item 5-point Likert-type self-report questionnaire [97]. The CTQ-SF consists of five subscales: physical abuse, sexual abuse, emotional abuse, physical neglect and emotional neglect. The questionnaire has demonstrated high [98] to acceptable [99] internal consistency, good convergent and discriminant validity [98] and good criterion-related validity [97]. The CTQ-SF will be administered at baseline.

#### Attachment style

The Attachment Styles Questionnaire (ASQ), a 24-item 5-point Likert-type self-report questionnaire [100] is used to generate individual measures of four attachment styles: secure, fearful, dismissive and preoccupied. The construct validity of the four scales is adequate as well as the reliability, except for the dismissing style [101]. The ASQ will be administered at baseline and 12 months after baseline.

#### Demographic characteristics

Demographic and general patient characteristics, such as treatment history, criminal history, medication use, age, gender, ethnicity, educational level and marital status, will be collected. A self-developed questionnaire will be administered at baseline, 12 months and 18 months after baseline.

#### Working alliance

The Working Alliance Inventory - short form (WAI-sf) [102, 103] a 12-item 5-point Likert-type self-report questionnaire, will be assessed to measure the therapeutic alliance of patient-therapist pairs. The WAI-sf measures three domains of therapeutic alliance: 1) patient-therapist agreement on the (value of) treatment goals, 2) patient-therapist agreement about the tasks (to achieve goals), and 2) the quality of the bond between patient and therapist. Psychometric properties are found to be adequate [102, 104]. The questionnaire will be filled out by both patient and coach at 3, 6, 9 and 12 months after baseline.

#### Intellectual disabilities

The Screener for Intelligence and Learning Disabilities (SCIL) is administered at baseline if official, recent information (not older than 2 years) about IQ levels of the patient is not available. The SCIL is a Dutch screening instrument that is validated and often used within similar populations to detect IQ levels under 85 [105]. The instrument consists of multiple assignments such as calculating, writing, reading, spelling, understanding of a proverb and drawing. Furthermore, the total score is also based on questions about the education level, use of intellectual disability services, reading behavior and the availability of family support. The SCIL demonstrated adequate sensitivity and specificity [105].

